## Abstract

**Background:**

Extreme obesity affects nearly 8% of Canadians, and is debilitating, costly and ultimately lethal. Bariatric surgery is currently the most effective treatment available; is associated with reductions in morbidity/mortality, improvements in quality of life; and appears cost-effective. However, current demand for surgery in Canada outstrips capacity by at least 1000-fold, causing exponential increases in already protracted, multi-year wait-times. The objectives and hypotheses of this study were as follows: 1. To serially assess the clinical, economic and humanistic outcomes in patients wait-listed for bariatric care over a 2-year period. We hypothesize deterioration in these outcomes over time; 2. To determine the clinical effectiveness and changes in quality of life associated with modern bariatric procedures compared with medically treated and wait-listed controls over 2 years. We hypothesize that surgery will markedly reduce weight, decrease the need for unplanned medical care, and increase quality of life; 3. To conduct a 3-year (1 year retrospective and 2 year prospective) economic assessment of bariatric surgery compared to medical and wait-listed controls from the societal, public payor, and health-care payor perspectives. We hypothesize that lower indirect, out of pocket and productivity costs will offset increased direct health-care costs resulting in lower total costs for bariatric surgery.

**Methods/design:**

Population-based prospective cohort study of 500 consecutive, consenting adults, including 150 surgically treated patients, 200 medically treated patients and 150 wait-listed patients. Subjects will be enrolled from the Edmonton Weight Wise Regional Obesity Program (Edmonton, Alberta, Canada), with prospective bi-annual follow-up for 2 years. Mixed methods data collection, linking primary data to provincial administrative databases will be employed. Major outcomes include generic, obesity-specific and preference-based quality of life assessment, patient satisfaction, patient utilities, anthropometric indices, cardiovascular risk factors, health care utilization and direct and indirect costs.

**Discussion:**

The results will identify the spectrum of potential risks associated with protracted wait times for bariatric care and will quantify the economic, humanistic and clinical impact of surgery from the Canadian perspective. Such information is urgently needed by health-service providers and policy makers to better allocate use of finite resources. Furthermore, our findings should be widely-applicable to other publically-funded jurisdictions providing similar care to the extremely obese.

**Trial Registration:**

Clinicaltrials.gov NCT00850356

## Background

Obesity currently affects 24% of Canadians[1] and is a chronic medical condition that leads to substantial morbidity,[2] premature mortality,[3] impaired quality of life (QOL),[4] and increased health care costs [5]. Obesity is most commonly defined according to body mass index (BMI), with BMI levels of 30-34.9, 35-39.9 and over 40 kg/m^2 ^corresponding to Class I, II and III obesity, respectively. Extreme obesity, defined herein as patients with moderate or severe obesity, is the fastest growing obesity subgroup affecting nearly 8% of Canadians [6]. Extreme obesity has increased in prevalence in Canada by 400% in two decades;[5] increases the risk of type 2 diabetes by up to 18-fold compared to normal-weight individuals;[2] shortens life expectancy by 8-13 years;[7] increases work-absenteeism;[8] and dramatically reduces QOL,[4] productivity,[9] and employability [10]. Health care expenditures in the 3% of the employed US population that are severely obese account for 21% of all health care costs associated with obesity [11].

### Bariatric Surgery for Extreme Obesity

Lifestyle modification (diet, exercise ± behavioural therapy) and pharmacotherapy for obesity each reduce weight by approximately 3-5% but are limited by poor long-term effectiveness and sub-optimal adherence [12,13]. In comparison, bariatric surgery leads to substantial weight reduction and has emerged an effective means to reduce weight and improve comorbidity in patients with extreme obesity [14]. Surgery is currently indicated in medically refractory patients with BMI levels of ≥ 40 kg/m^2 ^or BMI levels of ≥ 35 kg/m^2 ^with a major obesity-related comorbidity (e.g., hypertension, diabetes, sleep apnea) [14].

Bariatric procedures either involve stomach restriction alone or combined restriction plus intestinal diversion. The types of procedures performed have evolved over the past several decades and certain procedures, such as banded gastroplasty, have been abandoned due to poor long-term weight loss results. In Canada and globally, the most common operations performed are adjustable gastric banding (42%), Roux-en-y gastric bypass (40%) and sleeve gastrectomy (5%). Ninety percent of bariatric procedures are performed via laparoscopic (minimally invasive) techniques [15]. In gastric banding, the proximal stomach is encircled with an adjustable band that is progressively inflated to create a small, restrictive gastric pouch which reduces meal portions. In the roux-en-y gastric bypass, a highly restrictive gastric pouch is created and coupled with diversion of the upper small intestine. The sleeve gastrectomy procedure is performed by fashioning the stomach into an elongated tube and resecting the majority of the greater curve of the stomach.

### Outcomes Associated with Bariatric Surgery

Although no large scale, contemporary randomized controlled trials (RCTs) have examined the impact of surgery on cardiovascular morbidity or overall mortality, compelling data are available from high quality observational studies such as the Swedish Obesity Study (SOS), a matched cohort study of 2010 surgical and 2037 controls [16,17]. Compared to the poor long-term results of non-surgical therapy, surgery is the only therapy associated with substantial improvements in weight (averaging 33% after 2-3 years[18] and 16% after 10 years[16]); 15-year mortality rates (5.0% versus 6.3% in well-matched controls; HR 0.71; 95% CI 0.54 to 0.92);[19] 11-year incidence rates of first time cancers (HR 0.67; 95% CI 0.53-0.85);[17] and 7-year mortality rates from coronary artery disease (HR 0.41; 95% CI 0.21-0.78) and cancer (HR 0.40; 95% CI 25-0.65) [20]. In terms of other medical comorbidity, surgery increased remission rates for type 2 diabetes (73% versus 13%; p < 0.001; OR 5.5; 95% CI 2.2-14) in a 60-patient RCT;[21] and meta-analyses of primarily observational data has demonstrated that surgery is associated with resolution or improvement of type 2 diabetes, hypertension, dyslipidemia and sleep apnea in 70-86% of cases [18]. Additional studies demonstrate that surgery significantly (p < 0.05) improves psychosocial functioning,[22] quality of life,[23] and physical function [24].

In terms of Canadian data, a retrospective analysis of 1035 bariatric surgery patients from a single practice in Quebec reported 5-year excess weight losses of 61-75% following gastric bypass and banding [25]. In an earlier study, patients from this bariatric program (n = 1035) were also retrospectively compared with 5746 age and sex-matched controls identified using administrative data claims in Quebec (clinical variables such as height and weight were not available for controls) [26]. Mortality rates over 5 years were markedly lower in the bariatric surgery cohort compared to controls (0.68% versus 6.17%; RR 0.11, 95% CI 0.04-0.27) although the design of this study cannot rule out the very real likelihood that surgical selection bias (i.e., healthier and higher socioeconomic status patients with lower likelihood of surgical complications more likely to receive surgery) explains some if not most of these findings.

### Risks of Surgery

The complications of surgery can be divided into peri-operative and long-term complications. The totality of data suggests that the benefits of surgery far outweigh these risks [18,27]. Perioperative death rates are 0.1-0.5% and immediate postoperative complications (e.g., clots, cardiorespiratory events and wound infections) occur in 10% of individuals. Diversionary procedures increase the long-term risk of nutrient deficiency (up to 50% of patients) while gastric bands can slip (6% of patients) or erode (10%) necessitating re-operation [27]. Some long-term consequences of surgery such as micronutrient deficiencies (e.g., vitamin D deficiency and metabolic bone disease) are incompletely understood and require further study.

### Economic Evaluations of Bariatric Surgery

From the payor perspective and relative to the commonly cited thresholds of acceptability,[28,29] the long-term (20 years to lifetime) cost-effectiveness of surgery compared with non-surgical management appears attractive. Incremental cost-effectiveness ratios (ICERs) range from $5000 to $35 000 per quality-adjusted-life-year (QALY) [30]. The cost-effectiveness of surgery in patients with type 2 diabetes appears dominant (provides net health benefits and cost savings) compared to non-surgical interventions [31,32]. A recent Canadian economic evaluation performed by our group from the health care payor's perspective estimated that surgery is associated with ICERs of $8000-10 000/QALY over a lifetime horizon in Canada, with more favourable ICERs in subjects with greater obesity related comorbidity [30]. The only other additional published economic data from the Canadian perspective have been reported from a retrospective cohort study from Quebec. Surgery reduced health care utilization for a variety of disorders and was cost saving after 3.5 years compared to matched controls identified through administrative data claims [33].

However, there are limitations to the above studies. Economic studies based solely upon administrative data inputs do not include home and workforce productivity and patient borne costs. Furthermore, cost effectiveness analyses from the payor perspective do not examine such costs. Therefore, these additional data elements would provide a much more accurate picture of overall costs and benefits from a societal perspective.

### Demand, Access and Wait Times For Bariatric Surgery

Demand for bariatric surgery has increased at an exponential rate. The number of procedures performed globally has increased from 5000 in 1987-9 to 350 000 (63% in US/Canada) in 2009 [15,34]. In Canada, the annual number of procedures performed in public health care facilities in the past decade has increased nearly 19-fold to ~1500 procedures per year [35,36].

Despite this dramatic rise in uptake, the number of individuals potentially eligible for surgery greatly exceeds current surgical capacity. Given that the number of Canadians potentially eligible for surgery is 5.8% or 1.5 million (assuming a 2009 adult population of nearly 26 million),[37] and that about 1500 procedures are performed annually in Canada,[36] only 0.1% of potentially eligible patients are accessing surgery in this country. Therefore, actual demand may be orders of magnitude greater than current provision of surgery [38].

In Canada and elsewhere, surgery is available in both publicly and privately funded programs. Private surgery costs approximately $17 000 in Canada and is unaffordable to many [39]. However, wait times for publicly funded bariatric procedures in this country average 5 years,[40] and are similarly protracted in other public health care systems [41]. This clearly indicates a substantial demand-supply gap. A 2005 Ontario Ministry of Health report estimated demand at 3500 surgeries per year in that province, a 7-fold higher number than the 500 surgeries currently performed annually [42]. This necessitated outsourcing of procedures to the US at substantial cost;[42] and resulting in petitions from advocacy groups demanding improved access [43]. In 2009, Ontario announced $75 million funding to increase procedure numbers from 244/year to nearly 1500/year [38].

### Knowledge Gaps

In summary, the prevalence of extreme obesity has increased dramatically and bariatric surgery is the most effective treatment available. However, access to bariatric care in Canada is severely limited and wait times are lengthy. The ramifications of protracted wait times on health and health care costs have not previously been examined. In addition, data assessing the clinical and cost effectiveness of surgery in Canada are limited and further study is needed. Specifically, a comprehensive, population-based prospective assessment of the economic consequences from a health care payor, public payor (health care + other benefits such as unemployment insurance and other transfer payments), and societal (public payor, out-of-pocket costs, home and work productivity costs) perspective has not been performed to our knowledge in Canada or elsewhere.

Lastly, much of the prospective data evaluating bariatric procedures comes from the SOS study. However, vertical banded gastroplasty, which is now outdated, comprised nearly 70% of the procedures performed in SOS. More recent studies have evaluated gastric banding and gastric bypass and have reported similar results to SOS in terms of weight reduction and improvement in obesity-related comorbidities [44,45]. However, no prior studies comparing sleeve gastrectomy to medical management and APPLES results will help address this knowledge gap.

## Objectives and Hypotheses

The APPLES study is a population-based, prospective controlled study enrolling at minimum of 500 patients and designed to assess the impact of extended wait-times for bariatric care and examine the clinical and cost-effectiveness of bariatric treatment in the Canadian context.

The three major objectives of APPLES are:

1. To assess the impact of extended wait times for bariatric care by examining the two-year change in clinical, economic and humanistic outcomes in wait-listed patients. We hypothesize that patients will report progressive deterioration in these outcomes over time.

2. To determine the clinical effectiveness and changes in health-related quality of life associated with modern bariatric procedures and compare these outcomes to medically treated controls and untreated wait-listed controls. We hypothesize that surgery will markedly reduce body weight, decrease the need for unplanned medical care, and increase quality of life compared to controls.

3. To compare the costs associated with bariatric surgery to costs associated with medical and wait-listed controls over three years, from societal, public payor, and health care payor perspectives. We hypothesize that lower indirect, out of pocket and productivity costs will offset increased direct health-care costs resulting in lower total costs for bariatric surgery.

## Methods/design

### Overall Study Design

In this prospective cohort study, consecutive and consenting patients enrolled in the Weight Wise Regional Obesity Program and without a contraindication to surgery will be enrolled. The minimum enrolment sample size will include 150 surgical patients, 200 patients receiving intensive medical therapy and 150 patients wait-listed to enter the clinic (Figure 1). The number of patients enrolled in the medical arm is larger because we anticipate an increased rate of censoring in this study arm, as some of these patients will ultimately undergo bariatric surgery within the two-year follow-up period.

**Figure 1 F1:**
[figure not shown]
**APPLES Study Design**.

### Study Setting and Subject Recruitment

The Edmonton Weight Wise program is a comprehensive initiative established in 2005 designed to deliver integrated, patient-focused, evidence-based care to the Edmonton Zone of Alberta Health Services (AHS). This region is one of the largest integrated health delivery systems in Canada and includes a catchment population of approximately 1 million residents within greater Edmonton and an additional 600 000 residents in surrounding regions cared for by more than 1000 physicians, with an annual healthcare budget of almost two billion dollars [46].

Weight Wise includes a central, region-wide single-point-of-access referral system; community education and weight management sessions; and adult and pediatric bariatric specialty clinics. Adult specialty services are offered to patients with BMI levels of ≥ 35 kg/m^2 ^referred from a medical practitioner. By extrapolating from contemporary Canadian obesity surveillance data (i.e. ~8% of Canadians are moderately [BMI 35.0-39.9 kg/m^2^] or severely [> 40 kg/m^2^] obese), we estimate that over 125 000 adult patients within our region's catchment area has a BMI ≥ 35 kg/m^2 ^[6]. Community-dwelling patients referred for evaluation in the adult clinic are wait-listed at the time of referral (Figure 2). Currently, over 2000 adult patients are wait-listed for entry into the specialty clinic and their average wait may be up to several years in duration. Wait-listed patients are expected to attend community-based group education sessions prior to clinic entry. Otherwise, they receive no specific intervention.

**Figure 2 F2:**
[figure not shown]
**Structure of the Adult Component of Weight Wise**.

### Eligibility For Surgery

Within the adult specialty clinic, patients receive approximately 24-36 weeks of intensive lifestyle counselling (diet, exercise, behavioural modification), delivered by a multidisciplinary staff (internists, dieticians, nurses, physiotherapists, and psychologists) according to current recommendations [14]. Patients are seen approximately every 4-8 weeks. Patients interested in bariatric surgery are also evaluated for this procedure by the same multidisciplinary staff. Patients deemed to be appropriate candidates are subsequently evaluated by a bariatric surgeon. Patients with BMI levels ≥ 35-39.9 kg/m^2 ^and a major medical comorbidity (e.g., hypertension, type 2 diabetes, sleep apnea) or BMI levels ≥ 40 kg/m^2 ^are considered potential candidates for surgery. Absolute contraindications to surgery include pregnancy, uncontrolled psychiatric disease, active substance abuse or smoking (patients are required to quit prior to surgery), an active eating disorder (anorexia or bulimia), and high-risk for surgery medical status (e.g. severe coronary artery disease). Because of limited data documenting the benefits of surgery in patients younger than 18 years of age and evidence for possible harm in patients over 60,[47] procedures are not performed in these age groups. In order to access surgery, patients are also required to demonstrate commitment to attend scheduled appointments and adhere to lifestyle modification and behavioural therapy.

### Inclusion Criteria

1. Male or female patients in the Weight Wise Regional Obesity Program

2. 18-60 years old

3. BMI levels ≥ 35 kg/m^2 ^and a major medical comorbidity or BMI levels ≥ 40 kg/m^2^

4. Able to provide informed consent

### Exclusion Criteria

1. Pregnant or nursing

2. Currently participating in an obesity-related clinical trial or in whom protein-sparing low calorie diet is planned.

3. Contraindication to bariatric surgery and/or weight loss

4. Unable or unwilling to complete questionnaires or expected to experience difficulty with attendance of visits or completion of study data

5. Any other medical, social or geographic condition which, in the opinion of the investigators, would not allow safe completion of the study protocol

### Surgical Procedures Performed

Roux-en-Y gastric bypass, gastric banding and sleeve gastrectomy are all performed. Surgical techniques have been previously detailed [30,48,49]. Gastric banding is performed using the Swedish Adjustable Gastric Band (SAGB) Realize I/II(tm) (Johnson & Johnson/Ethicon Endosurgery, Cincinnati, Ohio) and sleeve gastrectomies are created over a 50 Fr bougie using staple line reinforcement throughout. Initially, gastric bypass was performed by hand sewing the gastrojejunostomy over a 34 Fr orogastric tube and positioning of the roux limb was retrocolic. Over the past two years, the technique has been modified and a 21 or 25 mm circular stapler is now used for the gastrojejunostomy pouch, with antecolic positioning of the roux limb. The roux limb is ~100 cm in length. The entero-enterostomy is created using varying techniques, including a combination of linear staplers and sutured closure.

### Follow-up

Follow-up visits will be scheduled every 6 months for two years and will be performed in-person or by telephone if necessary. The final two year follow-up visit will be performed in-person.

### Data Collection and Outcome Measures (Additional File 1 and Table 1)

**Table 1 T1:** Cost categories and details of source data for quantification and valuation of relevant costs

**Cost Category**^**1**^	Source Details	Units of Resources	Time Frame
1. Inpatient encounters	Administrative data	# of hospitalizations length-of-stay	Provided by fiscal year Referenced to time zero
2. Outpatient encounters	Administrative data	# encounters # procedures	Provided by fiscal year Referenced to time zero
3. Physician Fees	Administrative data	# encounters Provider specialty Service provided	Provided by fiscal year Referenced to time zero
4. Medications	Patient interview	Name Dosage, frequency & duration	Bi-annual
5. Weight Wise Clinic Visits	Administrative data and chart review	Personnel (nurses, dieticians, support staff) salaries Administrative and capital costs Supplies & equipment	Provided by fiscal year Referenced to time zero
6. Home Care & Long Term Care	Patient interview	Personnel (nurse, OT, PT, RT) salaries Disability aids (walker, bars, rails, etc.) Administrative and capital costs	Bi-annual
7. Transfer Payments	Patient interview	Unemployment insurance Disability benefits Assured Income for the Severely Handicapped (AISH)	Bi-annual
8. Employment status, absenteeism	Patient interview	Employment status in past year (# hours/week, # weeks) Absenteeism in past year (# days) Annual income (by quintile)	Bi-annual
9. Weight Loss Interventions	Patient interview	Weight loss program, meal replacements, physical trainer, exercise programs, alternative therapies, nutritional counselling, commercial program	Bi-annual
10. Mobility and Medical	Patient interview	Mobility aids, home modification/renovations, rehabilitation, paid personal assistance (household activities and home productivity, driving)	Bi-annual
11. Personal/Household Productivity	Patient interview as part of quality of life surveys	Capacity to perform household/domestic activities, personal care, and participate in leisure activities (Scalar) Paid/unpaid caregivers	Bi-annual

AHCIP = Alberta Health Care Insurance Plan. MACAR = Morbidity and Ambulatory Care Abstracting Record. DAD = Discharge Abstract Database. LOS = Length of stay. CIHI = Canadian Institute for Health Information. OT = occupational therapy. PT = physiotherapy. RT = respiratory therapy. SW = social worker.

^1^Health Care Payor perspective includes cost categories 1-6; Public Payor perspective includes cost categories 1-7 and Societal Payor perspective includes all costs.

After informed consent is obtained, baseline data collection for consenting patients will include the following: age, sex, race, marital status, employment status, household income quintile (≤ 20 K, 20-40 K, 40-60 K, 60-80 K, ≥80 K), general medical history and obesity-related comorbidities, smoking status (current, past, never), detailed current and past medications, weight, BMI, waist circumference, blood pressure, fasting lipids, fasting glucose, HbA1c, and liver enzymes.

Body weight will be measured using a validated, calibrated scale to the nearest 0.1 kilogram after the patient has emptied his/her bladder. Subjects will wear light indoor clothing with empty pockets and no shoes. Height will be measured using a wall-mounted stadiometre. A single reading taken using an automated blood pressure monitor and using an appropriately sized blood pressure cuff will be recorded with the subject seated in a chair and after five minutes of rest.

Repeat assessment of blood pressure, body weight, and cardiovascular risk factors (cholesterol profile, glycemic parameters) will be performed at 2 years.

Additional outcomes to be collected every 6 months will include:

1. **Household income and employment status**

2. **Quality of life and utility measurement**: Health related quality of life will be measured using validated, widely-used instruments. Generic and preference-based quality of life will be assessed using the Short Form-12 (SF-12[50]) and the EuroQol-5D (EQ-5D[51]) respectively. Obesity-specific quality of life will be assessed using the Impact of Weight on Quality of Life-Lite (IWQOL-Lite) [52].

3. **Patient satisfaction: **Satisfaction with medical care will be assessed using two questions, which will be rated on a 5-point Likert Scale:

a. The medical care I have been receiving is just about perfect

b. I am dissatisfied with some things about the medical care I received.

4. **Impact of Extended Wait Times: **The Waiting List Impact Questionnaire (WLIQ),[53] is a previously validated 47-item list of open-ended patient statements designed to assess the impact of extended wait-times in Canada for coronary bypass surgery and will be administered to wait-listed patients. This instrument has been modified for use in a bariatric population and items deemed not relevant to the bariatric setting were eliminated, resulting in a 40-item questionnaire. The instrument assesses general quality of life on a scale of 0-100 and also examines specific domains (physical stress, social support, frustration, employment status), which are serially evaluated by patients on a 5-point Likert scale. The degree of interest in bariatric surgery is specifically assessed.

5. **Edmonton Obesity Staging Score (EOSS)**:[54] EOSS is a recently proposed, preliminary staging system for obesity which is based upon the presence or absence of obesity-related comorbities. EOSS will be evaluated as a triage and prognostic tool within the APPLES cohort.

6. **Economic Data **(Table 1): Economic data will be collected for the year prior to enrolment and in the two years following enrolment. Two major data sources will be used to collect economic data.

a. **Administrative Data**: Linkage to AHS and Alberta Health and Wellness (AHW) administrative data sources will be performed according to previously described methods [55,56]. Because all permanent residents of Alberta are eligible for insurance by AHW and over 99.9% participate in this coverage, these administrative data will comprehensively capture patient-specific health care resource utilization. Data elements include vital statistics (mortality) and the following health care resources and costs: inpatient and outpatient encounters, physician billings, medical procedures, and emergency room visits (Table 1).

b. **Patient-Reported: **Second, in order to comprehensively capture all economic consequences and enable a societal perspective, each patient enrolled in the study will provide additional information retrospectively for the year prior to enrolment and prospectively for two years after enrolment on a bi-annual basis. Resource use will be identified through investigator and clinical experience as well as examination of comprehensive costs lists, and published literature (Table 1) [57]. There is no previously validated data collection instrument to measure these costs in obesity; thus, we have developed a comprehensive instrument using commonly used techniques [58,59]. Societal costs include costs of weight loss interventions (meal replacement, weight loss programs, alternative therapy, medications), mobility and medical costs (mobility aids, home modifications, rehabilitation, home care, housekeeping), workforce productivity (employment, absenteeism), home productivity (domestic chores, leisure activity, use of paid or unpaid caregivers) and transfer payments (unemployment insurance), and will be valued in accordance with Canadian guidelines [60].

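### Table 1's footnote assigns all medication and home-care cost to the payor by type of item, so any patient-paid part would be counted as payor cost

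*Protocol article*

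**What the plan says.** Table 1 of the protocol article lists eleven cost categories, and its footnote 1 maps them to three perspectives. The "Health Care Payor perspective includes cost categories 1-6"; the "Public Payor perspective includes cost categories 1-7 and Societal Payor perspective includes all costs".

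Categories 4 and 6 are both collected by patient interview. The units listed for medications are "Name Dosage, frequency & duration". Those for home care are personnel salaries, administrative and capital costs, and "Disability aids (walker, bars, rails, etc".

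The Knowledge Gaps section builds the perspectives up in layers. The public payor is health care plus benefits and transfers, and out-of-pocket cost appears only in the "societal (public payor, out-of-pocket costs, home and work productivity costs) perspective". The section on economic evaluations likewise says that payor-perspective analyses leave out patient-borne cost.

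Objective 3 hypothesises that "lower indirect, out of pocket and productivity costs will offset increased direct health-care costs".

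**The concern.** The footnote sorts costs by type of item. The Knowledge Gaps definition sorts them by who bears them. The two agree only if patients pay nothing towards categories 4 and 6.

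If patients do pay part, a change in drug or home-care use after surgery would be reported as a change in payor cost although some of it falls on the patient. The error can run in either direction, depending on whether use falls or rises.

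Two later uses depend on this allocation. The statistical section feeds costs into a model of the net impact of more surgery from each perspective. The Discussion would read unequivocal savings or neutrality for the public payor as showing surgery to be dominant and expansion a priority. Objective 3 itself weighs direct health-care cost against out-of-pocket cost, so the line between the two matters to the hypothesis.

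**Working it through.** The plan gives no figure for this point that could be reproduced. The check is a comparison of passages, then the algebra of the allocation.

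**Where the two categories sit**

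- Footnote 1: categories 4 and 6 lie within 1-6, so they are health-care-payor and public-payor costs, with no division by payer.
- Knowledge Gaps: out-of-pocket cost enters at the societal level only.
- Result: a patient-paid drug, home-care service or walker is a payor cost under the footnote and not a payor cost under the definition.

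**Where similar items sit**

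- Walkers, bars and rails are in category 6 (payor). Mobility aids and home modifications are in category 10 (societal only).
- Category 9 in Table 1 is "Weight loss program, meal replacements, physical trainer, exercise programs, alternative therapies, nutritional counselling, commercial program", with no medications. Item 6b on patient-reported data does place medications among weight-loss interventions, the heading of category 9. In Table 1 medications are category 4.
- Item 6b also places home care under "mobility and medical costs (mobility aids, home modifications, rehabilitation, home care, housekeeping", the heading of category 10. In Table 1 home care is category 6.
- Result: one walker, rail, home-care service or weight-loss drug could go to either of two categories with different perspectives, or be entered in both.

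**What the allocation does to the totals**

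Let C be the total category 4 and 6 cost per patient and P the part that patients pay.

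- Payor saving under the footnote = C(control) − C(surgery).
- Payor saving by who paid = [C(control) − P(control)] − [C(surgery) − P(surgery)].
- Overstatement of the payor saving = P(control) − P(surgery).
- The out-of-pocket saving is understated by the same amount.
- The two errors cancel in the societal total, which sums all eleven categories. Double entry of an item does not cancel; it would inflate the societal total.

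**Size**

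The patient-paid share is not given and could be anywhere from 0% to 100%. For scale only, assume that surgery cuts category 4 and 6 cost by $500 to $1500 a year, and that 30% to 70% is not paid by the payor, with the same share in both arms. Over two years:

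- low: 2 × 500 × 0.30 = $300
- high: 2 × 1500 × 0.70 = $2100

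Both inputs are assumptions without support in the documents. The cost sample-size paragraph plans to detect 20% of $12 183, that is 0.20 × 12 183 = $2437, which exceeds even the high value. That paragraph does not say which perspective its cost belongs to, so the comparison is loose.

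**The case against.** The other side has a fair case.

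- The footnote may say only which categories a perspective covers, not that amounts are booked regardless of payer.
- The relevant column of Table 1 is headed as units of resources, so payer and price would not be expected there. The purpose-built instrument and Additional File 1 are not shown.
- No passage says that patients pay for category 4 or 6 items. Collection by interview shows a different data source, not private payment.
- Salaries and capital costs look like provider inputs, and privately bought help has its own place in categories 10 and 11.

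Much of this stands, and it limits the point. Three stronger readings are tempting but unsupported:

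1. A reader might infer that the out-of-pocket saving cannot be measured at all. Categories 9 to 11 collect commercial programs, meal replacements, trainers, aids, home modification and caregivers, so the saving is measured incompletely.
2. A reader might infer from Table 1 that nobody asks who paid. With the instrument unseen, that is not established.
3. A reader might take item 6b's list of societal costs as contradicting the footnote. The perspectives are nested, and the same list names transfer payments, which are category 7 and public-payor. The list is therefore inclusive. It is evidence of unclear grouping, not of a contradiction.

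What the objection does not remove is the stated rule. Even if the instrument records the payer, the footnote makes no use of it, and as written it departs from the Knowledge Gaps definition.

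**Conclusion.** The point holds in a limited form. Footnote 1 assigns categories 4 and 6 whole to the payor perspectives, in conflict with the article's own placement of out-of-pocket cost. Any patient-paid part would be counted as payor cost, and the medication and home-care share of the hypothesised out-of-pocket saving could not be separated. The overlap of categories 4, 6, 9 and 10 adds a risk of misassignment or double counting.

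The health-care-payor and public-payor totals and the split between direct and out-of-pocket cost are affected. The hypothesis of lower total cost from the societal perspective is not affected by the payer allocation.

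The size is unknown. It is zero if patients pay nothing towards these categories, or if what they pay does not differ between arms. The illustrative dollar range is not an estimate. The point deserves correction before analysis because a policy conclusion is to be drawn from the public-payor total.

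**What to change.** - Change footnote 1 so that only payor-paid amounts in categories 4 and 6 enter the health-care-payor and public-payor totals. Patient-paid or privately paid amounts enter only the societal total, as out-of-pocket cost.
- If the instrument already has a payer item, use it. If not, add one for categories 4 and 6 at the remaining 6-monthly interviews; the Discussion has follow-up running to June 2012.
- For interviews already done, vary the payer share over a stated range in a sensitivity analysis. With 95% of enrolment complete by May 2010, this covers most baseline interviews and the retrospective year. Carrying back one recorded split would assume a constant share, which is doubtful if surgery changes drug and home-care use.
- Assign each aid, home-care item and weight-loss medication to one category only, and bring item 6b into line with Table 1.

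The cost is a slightly longer interview if the payer item is new, and a changed allocation rule. Payor savings may look less favourable as a result.
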